### 3.1 Study Participants

### 3.2 Inclusion Criteria

Adult, comatose patients admitted to NCCU with acute brain injury as a result of trauma with clinical indication for invasive monitoring of brain physiology (i.e. intracranial pressure, cerebral oximetry and parenchymal brain temperature, cerebral microdialysis) as part of their standard clinical management.

### 3.3 Exclusion Criteria

Patients with devastating injuries not expected to survive 24 hours will be excluded from the study. Lack of assent from consultee (see informed consent). Contraindications to cervical cooling (for example, an injury limiting access to the neck).

## 4. STUDY PROCEDURES AND INTERVENTIONS

### 4.1 Recruitment

Potential participants will be identified at the site of the investigation when they reach “level 2” of the standard clinical protocol (i.e. target temperature 35°C or below). Patients will be identified by the Principal Investigator and data will be captured and stored in our electronic medical record systems.

### 4.2 Informed Consent

All patients will be comatose and therefore lacking capacity to consent their participation to the study. Whenever possible, a next of kin acting as a “consultee” for the patient will be identified by the research team, and their opinion sought about their perceived participant's wishes and feelings in relation to the participating in the study. A member of the research team will approach the consultee to explain the study and its implications. Subjects are free to withdraw, or be withdrawn by their consultee if appropriate, at any point in the study, and they need not state a reason.

Where it proves impossible to contact consultees either in person, or by telephone, within 48 hours post admission, we will recruit subjects by identifying a nominated consultee, who is not part of the research team, such as the Consultant Neurosurgeon and Critical Care Physician in charge of the patient's care.

### 4.2 Study Assessments/Interventions

| Intervention or procedure                                | Total number of interventions/procedures received by each participant | Who will conduct the intervention/procedure |
|----------------------------------------------------------|-----------------------------------------------------------------------|---------------------------------------------|
| Randomisation                                            | 1                                                                     | Principal Investigator / LT                 |
| Selective Brain Cooling using the Neuronguard device     | 1                                                                     | Principal Investigator / LT                 |
| Off-line review of medical data and records for analysis | 1                                                                     | Principal Investigator / LT                 |

#### 4.3 Definition of End of Study

Data collection will be completed after 48 hours of monitoring of patient 10. The end of study is completion of data analysis.

### 5. SAFETY REPORTING

#### 5.1 Definition of Serious Adverse Events

A serious adverse event is any untoward medical occurrence that:

- Results in death,
- Is life-threatening,
- Requires inpatient hospitalisation or prolongation of existing hospitalisation,
- Results in persistent or significant disability/incapacity, or
- Other important medical events – in this cohort this would be uncontrollable intracranial hypertension

#### 5.2 Reporting Procedures for Serious Adverse Events

A serious adverse event (SAE) occurring to a participant should be reported to the REC that gave a favourable opinion of the study where in the opinion of the Chief Investigator the event was: 'related' – that is, it resulted from administration of any of the research procedures; and 'unexpected' – that is, the type of event is not listed in the protocol as an expected occurrence. Reports of related and unexpected SAEs should be submitted within 15 days of the Chief Investigator becoming aware of the event, using the NRES report of serious adverse event form (see NRES website).

### 6. STATISTICS

#### 6.1 Number of Participants

This preliminary study will enrol a small number of patients admitted to NCCU, Cambridge, UK. This is a pilot study assessing feasibility and proof-of-concept for a new approach to selective brain cooling, so no formal sample size calculation was indicated. This small scale pilot study was designed based on the indications of the i4i award evaluation Committee that requested the group to assess safety and feasibility of the approach before funding a full scale clinical trial.

#### 6.2 Sampling

We will enrol patients that meet the inclusion criteria consecutively.

#### 6.3 Analysis of Endpoints

Descriptive statistics will be used to report demographics and rate and nature of adverse events.

Non parametric tests will be used for between-group comparison of temperature data and paired data non parametric statistic tests for the brain/body differential temperature analysis.

Further exploratory data analysis of association between brain physiology, brain temperature, brain-body temperature gradients will be performed in the two groups to generate hypotheses for a larger clinical trial.

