## 3. STUDY DESIGN

This is a preliminary, proof-of-concept, randomised, interventional study.

The study will enrol at least 10 patients admitted to the Neurosciences and Trauma Critical Care Unit (NCCU, Addenbrooke's) following severe traumatic brain injury requiring invasive brain temperature monitoring and target temperature management as standard of care.

Brain temperature monitoring includes: ICP, brain oxymetry, microdialysis, haemodynamic variables. Physiological parameters and blood tests are also sampled on the ICM+ platform and local electronic medical record systems.

Randomisation of at least 10 patients will be made after the treating clinician has set a target temperature of 35°C. Using predetermined identical envelopes, patients will be assigned to two groups:

**Group 1, Standard Care (5 patients):** Medical and surgical management as per local treatment protocol (Figure). **Targeted temperature management induced by rapid infusion of ice-cold saline and maintained by automated cooling blankets.**

**Group 2, Experimental Care (5 patients):** Patients allocated to group 2 will receive the same treatment as those in group 1, with the exception of maintenance of **target temperature by using selective cervical cooling.**

Cervical cooling will be delivered with a purpose built prototype developed by Neuronguard. Brain temperature, core temperature (bladder or oesophageal), ICP and other physiological parameters will be continuously monitored and captured digitally as per standard local practice. Temperature targets are determined by the treating clinician, they will be recorded by a chart at the bedside, updated hourly, with brain temperature targets expressed as absolute values  $\pm 0.5^{\circ}\text{C}$ . Monitoring will continue for 48 hours, irrespective of temperature targets (i.e. to include rewarming, if indicated).

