### 7.1 Data Protection and Patient Confidentiality

Data is collected and stored on the Trust safe server. Data exported from the Trust server will be anonymized and stored on encrypted computers. All audio/visual will contain no patient identifiable features. Pictures will be taken to document any adverse reaction connected to this new approach.

The data generated by the study will be analysed on NHS computers of the Cambridge University Hospital by the Principal Investigator and the appointed consultant of bio-statistics (if required). Physiological data will be anonymized and encrypted. Data will be stored in a firewall and password protected, secure NHS drive at the Addenbrooke's Hospital for a minimum of 6 years and possibly indefinitely in accordance with good research practice. Only the Principal Investigator will continue to have access to the data.

Cambridge University Hospital NHS Foundation Trust will keep identifiable information about participants for 5 years after the study has finished.

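### Section 6.3 gives the brain-core differential a paired test although its objective is a between-group comparison, and it leaves the unit of analysis open for 48 hours of continuous temperature data

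*Protocol*

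**What the plan says.** Section 6.3 is the only analysis text in the protocol. Adverse events and demographics are described. For temperature, one sentence names two methods: "Non parametric tests will be used for between-group comparison of temperature data and paired data non parametric statistic tests for the brain/body differential temperature analysis".

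The secondary objectives (synopsis and Section 2.2) list two temperature endpoints, the brain-to-core differential and brain temperature within target. Both are marked as comparisons between the groups. The synopsis, under Study Design, also counts the brain-body gradient among the primary outcomes.

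Section 3 describes the data and the allocation. Brain and core temperature "will be continuously monitored and captured digitally as per standard local practice", and "Monitoring will continue for 48 hours, irrespective of temperature targets". The patient is the randomised unit: "Using predetermined identical envelopes, patients will be assigned to two groups", with 5 in each group and at least 10 in all. Targets are charted hourly, as a value ±0.5°C.

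No section defines a per-patient summary, names the unit of analysis, or mentions repeated measurements.

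**The concern.** There are two linked problems.

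First, the test named for the differential does not match its objective. A paired test of brain against core asks whether the two temperatures differ within the patients analysed. The objective asks whether that difference is larger with cervical cooling than with systemic cooling. A gradient present in both arms would satisfy the paired test and say nothing about the device.

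Second, with continuous capture and no stated unit, the same sentence allows two very different analyses. One uses about 10 patient values. The other uses hundreds or thousands of readings, which are correlated within a patient. Only the first rests on what was randomised.

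The differential is the proof-of-concept evidence, and the synopsis makes the next, larger study depend on showing selective cooling. A finding that does not contrast the arms, or that arises from ordinary differences between patients, would weaken that decision.

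**Working it through.** The protocol states no sample size calculation, alpha or effect, so there is no figure to reproduce.

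**Inputs from the protocol:** 5 v 5 patients (synopsis; Section 3), 48 hours of monitoring (Section 3), test families (Section 6.3).

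**Assumptions, not in the protocol:** two-sided alpha 0.05; m = 48 hourly readings per patient; lag-one autocorrelation r between hourly readings; share s of total variance lying between patients; no device effect.

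**Step 1. The paired test at patient level.** With n pairs, the smallest two-sided signed-rank p is 2/2ⁿ.

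- 5 device patients: 2/2⁵ = 2/32 = 0.0625, so 0.05 cannot be reached whatever the device does.
- All 10 patients: 2/2¹⁰ = 2/1024 = 0.002, but both arms are then combined and nothing is compared between them.

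Within the device arm, this test could therefore fall below 0.05 only if readings, not patients, were the pairs.

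**Step 2. What pooling readings would do.** The variance of a group mean, relative to independent readings, is inflated by

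D = m·s + (1 − s)·f, where f = 1 + 2·Σ(1 − k/m)·rᵏ for k = 1 to m − 1.

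The rejection rate of a nominal 5% test is then about 2·[1 − Φ(1.96/√D)]. For m = 48:

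| r | s | f | D | 1.96/√D | Rejection rate |
|---|---|---|---|---|---|
| 0 | 0 | 1.00 | 1.00 | 1.96 | 0.05 |
| 0.1 | 0 | 1.22 | 1.22 | 1.78 | 0.08 |
| 0.3 | 0 | 1.83 | 1.83 | 1.45 | 0.15 |
| 0 | 0.01 | 1.00 | 1.47 | 1.62 | 0.11 |
| 0.8 | 0 | 8.17 | 8.17 | 0.69 | 0.49 |
| 0.8 | 0.1 | 8.17 | 12.15 | 0.56 | 0.57 |
| 0.8 | 0.3 | 8.17 | 20.12 | 0.44 | 0.66 |
| 0.8 | 0.5 | 8.17 | 28.08 | 0.37 | 0.71 |

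Example for the last row: 48 × 0.5 + 0.5 × 8.17 = 28.08.

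Simulations of this model with a Mann-Whitney test on pooled readings agree. With s = 0 they gave about 7% to 8% at r = 0.1 and 12.5% to 15% at r = 0.3. At r = 0.8 they ran from 48% to 51% with s = 0 up to 71% to 75% with s = 0.5.

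A pooled signed-rank test in the 5 device patients behaves alike. With r = 0 and s = 0.05, 0.1, 0.3 and 0.5 it rejected in 0.28, 0.40, 0.62 and 0.69 of simulated trials. The formula gives 0.28, 0.41, 0.61 and 0.69.

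**Step 3. One value per patient, compared between arms.** There are 252 ways (10 choose 5) to split 10 patients 5 and 5.

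- Smallest two-sided p: 2/252 = 0.008.
- The largest attainable p below 0.05 is at U ≤ 2: 8/252 = 0.032. The next step is 14/252 = 0.056.

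Without ties, the true size is therefore 0.032 whatever the correlation within patients.

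**The case against.** The strongest reply is that Section 6.3 only names a family of methods, and that reducing a 48-hour stream to one value per patient is normally left to an analysis plan. Non-parametric tests include exact tests on patient values, and paired data could mean one brain and one core value per patient. Between-group temperature data could also be read to include the differential. This is a pilot with no formal sample size (Section 6.1), its objectives are worded as description, and no error rate is claimed.

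Much of that stands. A reader might infer that the protocol plans to test individual readings as independent. It does not say so; continuous capture describes the monitoring, not the analysis. Nor does the remark in Section 7.1 that data are analysed "by the Principal Investigator and the appointed consultant of bio-statistics (if required") settle the unit, since that passage concerns who handles data.

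A reader might also infer that any correlation at all gives a very high false-positive rate. The table shows otherwise: weak correlation inflates the rate modestly.

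The mismatch over the differential is not silence, however. Section 6.3 singles that endpoint out and gives it a paired test, while Section 2.2 asks for a comparison between groups. The generous reading is possible, but the text does not secure it. Pilot status does not remove the point either, because Section 6.3 commits to tests as well as description.

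**Conclusion.** The point holds in limited form. The method named for the brain-core differential does not answer the between-group question set for it. At patient level in the device arm, it cannot go below p = 0.0625. The unit of analysis is open where that choice matters.

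The size of the second problem is conditional on readings being pooled. The false-positive rate would then be about 8% to 15% at weak autocorrelation and about 50% to 70% at autocorrelation 0.8. This assumes hourly readings, alpha 0.05 and correlations that the protocol does not give. It shows what the wording permits and is not a forecast of the analysis.

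The concern is confined to the temperature and proof-of-concept inference; adverse-event reporting is unaffected. It is a cheap and worthwhile correction, not a flaw that undermines the study.

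**What to change.** Amend Section 6.3 to state the following:

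- The randomised patient is the unit of analysis for both temperature endpoints.
- Each patient contributes one value per endpoint: the mean brain-core differential over the monitored period, and the percentage of monitored time with brain temperature within target ±0.5°C.
- The randomised groups are compared on these values with an exact Mann-Whitney or permutation test. A permutation version copes with ties, which are possible for the percentage in target.
- The paired brain/body analysis is kept within each arm, on one pair per patient, as descriptive support only.

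This changes a sentence or two and uses data already collected. The price is larger p-values and wider intervals, which reflect about 10 patients and not the number of readings. With 5 v 5, complete separation of the arms would still give p = 0.008.

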| Planned Sample Size (if applicable) | 
At least 10 patients will be randomly allocated to two groups using pre-allocated sealed identical envelopes.
 
Standard care (5 patients): standard clinical protocol;
                                                                                                                                                                                                                                                                                                                                                                                                                                                                                                                                                                                                                                                                                                                                                                                                                                                                                                                                                                                                                                                                                                                                                                                                                                                                                                                                                                                                                                                                       |

|                             |                                                                                                                                                                                                                                                                                                                                                                                                                                                                                                                     |

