## 2. OBJECTIVES

### 2.1 Primary Objective

**Safety.** Describe number and severity of complications associated with induction and maintenance of hypothermia using selective cervical cooling:

- failure to maintain the brain within target temperature;
- number of instances where external cooling blankets or ice-cold saline had to be used as a rescue strategy to achieve target temperature;
- duration and severity of cerebral hyperthermia;
- any other adverse event;

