### 2.2 Secondary Objectives

**Proof of concept.** Describe the ability of the device to deliver selective brain cooling, and its effectiveness:

- differential brain-to-core temperature as evidence of selective cooling (between-group comparison);
- brain temperature within target parameters (between-group comparison);

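### For the between-group comparison of brain temperature within target, section 6.3 names only a test for difference, which at about 5 v 5 cannot show adequate control and yields no effect size

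*Protocol*

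**What the plan says.** Section 2.2 of the Protocol sets out to describe the device's ability to cool the brain selectively and its effectiveness. It lists two between-group comparisons: the brain-to-core temperature differential, and brain temperature within target. The Study Design row of the Synopsis also places keeping the brain in target among the primary outcomes.

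Section 6.3 gives the method: "Non parametric tests will be used for between-group comparison of temperature data", with paired non-parametric tests for the brain/body differential. It assigns descriptive statistics to demographics and adverse events, and adds exploratory analysis of associations to generate hypotheses for a larger trial. It states no significance level, estimate, interval or threshold for the in-target comparison.

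On size, the Synopsis says "At least 10 patients will be randomly allocated to two groups using pre-allocated sealed identical envelopes", and section 3 gives 5 patients to each group. Section 6.1 says that "no formal sample size calculation was indicated".

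Section 2.1, the primary safety objective, separately describes complications of cervical cooling. Its list includes "failure to maintain the brain within target temperature", the number of times systemic cooling was needed as rescue, and the duration and severity of cerebral hyperthermia.

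**The concern.** In the experimental arm, cervical cooling takes the place of blankets for maintaining target temperature (section 3). On the in-target endpoint the device need not beat systemic cooling; a reader will want to know whether it does about as well. A test for difference does not answer that. With few patients it tends to return a non-significant result whether the two methods are alike or the device is moderately worse. The brain-to-core differential is not affected in the same way, because there a non-significant result counts against the device.

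The choice also fits poorly with the protocol's own aims. Section 2.2 says the purpose is to describe, section 6.1 says the trial was not sized, and the pilot exists to inform a decision on a full-scale trial. That trial will need an effect size and a measure of spread, and a p-value supplies neither.

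**Working it through.** The protocol states no power or sample size figure, so there is none to reproduce. The check asks what the named test can do at the stated size.

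**Inputs from the Protocol.** 5 patients per arm (section 3); a non-parametric between-group test (section 6.3); no sizing calculation (section 6.1).

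**Assumptions, because the Protocol does not state them.** Wilcoxon rank-sum (Mann-Whitney) test, exact, two-sided, level 0.05, one summary value per patient; normal values with equal SD unless stated otherwise.

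**Step 1: rejection rule.** There are C(10,5) = 252 equally likely rank arrangements under the null. The numbers giving U = 0, 1, 2, 3 are 1, 1, 2, 3.
- P(U ≤ 2) = 4/252 = 0.0159, so two-sided 8/252 = 0.0317.
- P(U ≤ 3) = 7/252 = 0.0278, so two-sided 14/252 = 0.0556, which exceeds 0.05.

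The test rejects at U ≤ 2 or U ≥ 23, and its true size is 3.2%.

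**Step 2: power against a shift, by simulation (100,000 trials per point).**

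| Device worse by | Power, 5 v 5 |
|---|---|
| 0.5 SD | 7% |
| 0.8 SD | 14% |
| 1.0 SD | 21% |
| 1.5 SD | 43% |
| 1.6 SD | 48% |
| 1.7 SD | 53% |
| 2.0 SD | 68% |
| 2.5 SD | 86% |

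Power passes 50% at about 1.65 SD and 80% at about 2.3 SD. More than 10 patients are allowed; with 8 per arm, power is 44% at 1 SD and 77% at 1.5 SD.

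**Step 3: share of time in target (beta-distributed; all means and SDs assumed).**

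| Control v device | SDs (points) | Power |
|---|---|---|
| 90% v 80% | 8, 15 | 14% |
| 80% v 60% | 20, 20 | 24% |
| 85% v 65% | 20, 20 | 29% |
| 90% v 75% | 8, 15 | 33% |
| 90% v 70% | 10, 20 | 34% |
| 80% v 50% | 20, 25 | 35% |
| 90% v 60% | 10, 20 | 67% |

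In these scenarios a 20-point deficit is missed about two times in three or more often. A 30-point deficit may be missed or found, depending on spread.

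**Step 4: what an interval would show.** Inverting the same test gives the exact Hodges-Lehmann interval: the third smallest to the third largest of the 5 × 5 = 25 pairwise differences. Coverage is 1 − 8/252 = 96.8%, and the simulated mean width is about 3.3 SD. With an assumed SD of 20 points, that is 3.3 × 20 = 66 points.

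**Step 5: whether a formal non-inferiority test is an alternative.** With one-sided 0.025, 80% power and no true difference, n per arm = 2(1.96 + 0.84)²/margin², with the margin in SDs. A 1 SD margin needs 16 per arm and a 0.5 SD margin needs 63. At 5 per arm the smallest margin that could be ruled out with 80% power is (1.96 + 0.84)√(2/5) = 1.77 SD. It is not feasible here, so estimation is the realistic choice.

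**The case against.** Four points can be made for the protocol.

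First, a reader might infer that holding target is judged only by a significance test. The documents do not support that. Section 2.1 describes failures to hold target, rescue use and hyperthermia under the device, and needs no test to do so. This stands: a very poor device would show there. What those measures do not supply is a comparison with systemic cooling, since the objective is worded for cervical cooling alone.

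Second, a reader might infer that a clearly worse device will usually come out as no different. That holds for deficits up to about 1.6 SD but fails beyond about 1.65 SD; at 2 SD the device is detected 68% of the time.

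Third, a reader might infer that the protocol will treat non-significance as comparable control. It nowhere says so and sets no equivalence or non-inferiority aim. Its one stated condition for going further, in the Synopsis, concerns selective cooling, where low power works against the device. The harm is therefore a possible misreading, not a stated rule.

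Fourth, low power is no fault in a declared pilot, and estimators and intervals are often left to a SAP. The first part stands. On the second, naming tests does not forbid reporting medians or intervals, so the missing interval alone would not be a finding. But 6.3 does fix a method for this comparison, and it is one that serves the descriptive aim of 2.2 poorly.

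Rescue systemic cooling in the experimental arm cuts both ways. It can pull brain temperature back towards target and shrink the tested difference, and it makes the rescue count an important companion to the comparison.

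**Conclusion.** The concern holds as a minor point about the choice of analysis. The one method section 6.3 names for the in-target comparison cannot, at about 5 v 5, show that the device controls temperature adequately, and a p-value from it would leave the larger trial without an effect size. The chance of missing a real deficit is 79% at 1 SD (100 − 21), about even at 1.65 SD, and 32% at 2 SD (100 − 68). These figures rest on an exact two-sided rank-sum test at 0.05 with one value per patient and normal data. The time-in-target scenarios rest further on assumed means and SDs. The finding does not call for more patients, and it does not say that the trial would overlook a device that plainly fails.

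**What to change.** In section 6.3, or in the SAP if the protocol is not to be amended:

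- Make the main reported result for each between-group temperature endpoint the Hodges-Lehmann difference with its exact interval (96.8% coverage at 5 v 5), together with a plot or listing of every patient's value.
- Present the in-target result alongside the rescue counts.
- Label any p-value supplementary, and state that a non-significant result is not evidence that the device controls temperature comparably to systemic cooling.

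This uses the data already planned and adds no patients. It is a change of wording only. The downside is that the published interval will be wide, about 3.3 SD, which is a fair picture of what 10 patients can show.

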| Study Design                        | 
Interventional, randomised, first-in-human, proof-of-concept pilot study comparing two methods of brain temperature management following brain injury: total body cooling (standard care) and selective cervical cooling (experimental).
 
Target temperature management delivered by means of systemic cooling is standard of care for brain protection following severe TBI. This is typically delivered by means of body surface cooling and infusion of ice-cold crystalloids. Systemic cooling is known to be associated with cardiac, respiratory, renal and infective complications.
 
This study will test the feasibility and safety of cervical cooling to deliver selective brain cooling in a small number of brain injured patients – as instigated by the NIHR i4i panel.
 
Brain temperature and systemic temperature will be monitored as part of standard clinical care. Temperature management will be delivered by means of standard care (systemic cooling) or by selective cervical cooling using a purpose-built prototype, developed and provided by Neuronguard.
 
The primary outcomes will be safety of the experimental strategy, its ability to maintain brain temperature within temperature targets set by the treating physician and the proof-of-concept that cervical cooling can induce selective brain cooling (i.e. quantified as the brain-body temperature gradient).
 
If cervical cooling shows the ability to deliver selective brain temperature, the strategy will be tested in subsequent clinical study on a larger sample to describe its safety profile against systemic cooling.
 |

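### Section 6.3 gives the brain-to-core difference a paired test, although Section 2.2 and the Synopsis declare it a between-group comparison

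*Protocol*

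**What the plan says.** The secondary objective in Section 2.2, repeated in the Synopsis, is proof of concept. Its first item is "differential brain-to-core temperature as evidence of selective cooling (between-group comparison", with the parenthesis naming the type of comparison. The design text of the Synopsis gives the same quantity more weight, listing among the primary outcomes the "proof-of-concept that cervical cooling can induce selective brain cooling (i.e. quantified as the brain-body temperature gradient".

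Section 6.3 then divides the tests within one sentence. The first half reads "Non parametric tests will be used for between-group comparison of temperature data". The second half assigns "paired data non parametric statistic tests for the brain/body differential temperature analysis". The paired test is not named. No significance level or sidedness is given.

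On numbers, Section 3 has "Group 1, Standard Care (5 patients" and "Group 2, Experimental Care (5 patients" in the two headings. The Synopsis gives the total as a minimum: "At least 10 patients will be randomly allocated to two groups". Section 4.3 treats ten as the working total: "Data collection will be completed after 48 hours of monitoring of patient 10".

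**The concern.** The objective and the analysis section describe different comparisons for the same quantity. The objective asks whether the difference between brain and core is shifted by cervical cooling relative to systemic cooling. A paired test of brain against core asks whether the two temperatures differ inside the same patients, and a yes to that does not answer the first question.

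This is more than a detail that a protocol may leave to a statistical analysis plan. The protocol names a family of tests for this endpoint, and that family does not match its own objective.

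At stake is the result on which the next study depends. The Synopsis makes the larger study conditional on the device showing that it can cool the brain selectively, and Section 6.1 says the funder wanted this pilot before paying for a full trial. If Section 6.3 is followed literally, the figure reported for that purpose does not estimate the device effect against standard care.

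**Working it through.** The plan gives no power, significance level or calculated sample size, so it has no figure to reproduce.

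**What each test asks.** Let D be a patient's brain temperature minus core temperature, with D_E in the experimental arm and D_S in the standard arm.

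- Paired test within the device arm: is the centre of D_E zero?
- Between-group test, as in Section 2.2: is the centre of D_E minus the centre of D_S zero?

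Two cases separate them:

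- *Shared difference, no device effect.* D_E = D_S = g, with g not zero. The device effect is g − g = 0, but the paired test sees g and can call it selective cooling.
- *Device removes an existing difference.* D_S = g and D_E = 0. The device effect is 0 − g = −g, but the paired test sees zero and reports nothing.

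The documents do not give the usual size or sign of g, so both cases are illustrations of what the test cannot distinguish.

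**Size of the first case.** Simulation with normal differences, SD 1, a common shift of 1.5 SD in all 10 patients, no device effect, exact signed-rank test at two-sided 0.05, 2,000 runs: rejection in about 98%. A significant paired result over both arms is therefore compatible with no device effect at all.

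**Secondary: what five patients allow.** Assumptions not in the protocol: two-sided 0.05, exact tests, one value per patient, no ties or zeros.

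- Signed-rank (or sign) test, n patients: smallest p = 2/2^n. For n = 5, 2/32 = 0.0625.
- Mann-Whitney test, n1 against n2: smallest p = 2/C(n1+n2, n1). For 5 against 5, 2/252 = 0.0079.
- For 5 against 5, U ≤ 2 gives 8/252 = 0.032, and U ≤ 3 gives 14/252 = 0.056. The rejection region is thus U ≤ 2 or its mirror image.

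| Situation | Smallest two-sided exact p |
|---|---|
| Paired, 5 device patients | 0.0625 |
| Paired, 6 device patients | 0.031 |
| Paired, both arms pooled, n = 10 | 0.0020 |
| Between groups, 4 against 5 | 0.016 |
| Between groups, 5 against 5 | 0.0079 |
| Between groups, 6 against 6 | 0.0022 |

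One-sided, the paired minimum with five patients is 1/32 = 0.031. The uncorrected normal approximation would print 0.043 (0.059 with continuity correction), but the exact value is 0.0625.

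Under the same assumptions (normal differences, SD 1, 2,000 runs), the between-group test rejected in about 21%, 69% and 95% of runs at true differences of 1, 2 and 3 SD. The paired test in the device arm rejected in none, as the floor requires.

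**Baseline subtraction.** With equal variances, a change from baseline has variance 2σ²(1 − ρ), which is below σ² only if the baseline correlation ρ exceeds 0.5. For an assumed effect of 0.5 °C and SD 0.5 °C, simulated power of the 5-against-5 test is about 21% without a baseline. With it, power is about 33%, 47% and 77% at ρ = 0.7, 0.8 and 0.9, but about 15% at ρ = 0.3 and 12% at ρ = 0. The protocol gives no value of ρ.

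**The case against.** **The paired test has a purpose.** The end of Section 1 lists, among the things to be assessed, whether the device can produce and hold a difference between brain and body. That is a within-patient question, and pairing addresses it. This stands: the paired analysis should be kept in a supporting role, not deleted.

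**The differential is itself temperature data.** On a lenient reading, the first half of the sentence in Section 6.3 already covers a between-group test of the difference, and the paired test is an addition. Section 6.3 also plans exploratory work on gradients in the two groups. A reader might infer from the concern that the control arm goes unused, and the text does not support that. But the sentence names the differential separately and gives it the paired test, so the lenient reading has to be supplied by the reader.

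**No significance threshold is set.** Both objectives are worded as descriptions, Section 6.1 disclaims a formal sample size, and no go/no-go rule rests on a p-value. A reader might infer that the proof of concept can never be significant. That goes too far. The 0.0625 floor needs a two-sided 0.05 level, an exact test, the device arm alone and exactly five patients, and the total is stated as a minimum.

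**Pooling of readings.** With continuous monitoring, a reader might fear that serial readings will be treated as independent patients, which would inflate the false-positive rate severely. Nothing in the protocol plans this, and the unit of analysis is commonly left to the analysis plan. It is no part of the finding.

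**Conclusion.** The point holds as a contradiction between Section 6.3 on one side and Section 2.2 and the Synopsis on the other. Followed literally, Section 6.3 tests whether brain and core differ within patients. That cannot show the effect of cervical cooling relative to standard care, whatever the sample size. This conclusion rests on the wording alone and needs no assumed figure. The 98% rejection rate illustrates its size under an assumed shared difference of 1.5 SD.

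The p-value floors (0.0625 paired in five device patients, 0.0079 for five against five) are correct but secondary, because they depend on a two-sided 0.05 level that the protocol never states. It would be wrong to conclude that the result must be either non-significant or an artefact of pooled readings: a one-sided test, a sixth device patient or a paired test over both arms would each escape that choice. The last would still not isolate the device effect.

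**What to change.** Amend Section 6.3 to say that:

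- the brain-to-core difference is summarised as one value per patient, for example the mean brain-minus-core difference over the 48-hour monitoring window;
- these values are compared between the randomised groups with an exact Mann-Whitney test;
- the Hodges-Lehmann difference is reported with its exact confidence interval (for 5 against 5, the interval matching the U ≤ 2 region has coverage 1 − 8/252 = 96.8%);
- the paired brain-versus-core analysis is reported within each arm, as a supporting description of whether a difference was produced.

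Because the experimental arm may receive systemic cooling as rescue, the between-group result should be described as the effect of the allocated strategy.

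Subtracting a pre-randomisation baseline is optional. It helps only if the baseline correlation exceeds 0.5, and the protocol does not state that both temperatures are captured in a defined window before randomisation. If it is wanted, it should be specified before data are seen.

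The cost is one or two sentences. No new data are needed for the main change, since Section 3 already provides for continuous digital capture of brain and core temperature. The price of the between-group test is modest power at this size: about 21% at a true difference of 1 SD. The estimate and interval should therefore carry the report.
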